#### Aim 1—Hypotheses 1(a) and 1(b)

Outcome measure trajectories will be plotted by randomization arm over time. Each outcome measure will be summarized at each assessment time by treatment arm using descriptive statistics. Comparisons between randomization arms with respect to changes in symptom outcomes will be based on specific coefficients from time-by-arm interactions added to the general LMM template described above in the *General Description* section. Specifically, the model will include all time points (categorical) at which the outcome was assessed (baseline and weeks 4, 8, 16, and 26), and the time-by-arm interaction will include multiple coefficients corresponding to the time-by-arm interaction at each discrete postbaseline time point. However, statistical inferences will focus on the interaction coefficients at 8 and 26 weeks, which are interpreted as the differences between arms in change from baseline to 8 and 26 weeks, respectively. For hypothesis 1(a), the 2 primary end points are HADS anxiety score changes at 8 weeks and 26 weeks. On the basis of the LMM coefficients for the time-by-arm interaction at weeks 8 and 26, 2 tests will be performed to determine whether MT is noninferior to CBT at reducing the HADS anxiety subscale score within a noninferiority margin of 0.35 SD for both comparisons. The noninferiority of MT to CBT will be tested at a significance threshold of *P*<.025 for each comparison, controlling the overall type I error at *P*=.05 for the primary end point comparisons. For hypothesis 1(b), a similar LMM evaluating BFI scores over time will be used to test whether the MT arm had significantly greater improvement in fatigue (BFI score) compared with the CBT arm at weeks 8 and 26. In contrast to the primary end point noninferiority comparisons, these tests will be superiority tests. For other comorbid symptoms (eg, depression and insomnia) and quality of life, the methods described for hypothesis 1(b) will be used to compare the treatment arms. Given that a small number of cancer survivors may experience disease recurrence during the 26-week study, sensitivity analyses will be performed, excluding those individuals who experienced a recurrence during the study period. These sensitivity analyses will not replace the primary analysis.

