### Analytical Approach

#### General Description

Analyses will be conducted using the intention-to-treat principle (ie, participants will be analyzed according to their randomly assigned treatment group regardless of dropout or treatment adherence status). Given that CBT is widely recognized as a first-line therapy for anxiety, the study team opted to test the noninferiority of MT to CBT, with the goal of understanding whether MT can be an appropriate treatment option for patients who lack CBT access or do not wish to pursue CBT. To provide complementary information for treatment decision-making, the study team will also test which intervention is superior for addressing fatigue and other symptoms co-occurring with anxiety. For all specific aims, the main analytical tool will be a linear mixed-effects model (LMM) because the primary outcome (anxiety) and secondary outcomes (fatigue, depression, insomnia, pain, cognitive dysfunction, and health-related quality of life) are repeated continuous outcomes over time [142]. This statistical procedure takes into account within-subject correlations from repeated measurements in the same subjects and allows the estimation of between-group differences without necessitating the exclusion of participants with missing data. The general template of each LMM will model the outcome as a function of the treatment arm and assessment time (categorical), controlling for the randomization stratification variables (baseline anxiety medication use, preferred language, and study site) and including a subject-specific random intercept. The general LMM template will be tailored to test the specific aim hypotheses by adding interaction terms (eg, time-by-intervention) and additional covariates of interest to the model and by reparametrizing the assessment time variable to focus on specific contrasts.

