#### Sample Size and Power

The sample size is based on the primary hypothesis that MT is noninferior to CBT for anxiety reduction at weeks 8 and 26. Two tests will be performed to determine whether MT is noninferior to CBT at reducing HADS anxiety at weeks 8 and 26, each with a noninferiority margin of Cohen *d*=0.35 SD for both comparisons. These comparisons will be based on the LMM coefficients for the time-by-arm interaction at weeks 8 and 26; however, the power calculation is based on 2-sample *t* tests of differences between the arms in their change scores. Therefore, the power estimate is conservative, that is, in the LMM-based analysis, there will be slightly higher power than the power calculation presented below, with all other assumptions held constant. Assuming 150 participants are randomized to each arm, 15% attrition, and a 1-sided significance threshold of *P*=.025 (controlling the overall type I error at 0.05 for our 2 primary end point comparisons), there will be 80% power to find MT noninferior to CBT with respect to the HADS anxiety subscale scores at weeks 8 and 26 within a noninferiority margin of Cohen *d*=0.35 SD.

The noninferiority margin was informed by a large study that used multiple rigorous methods to empirically estimate a difference of 1.7 points as the MCID for the HADS scales [120]. In preliminary data from CBT recipients with baseline HADS anxiety subscale scores ≥8, the SD for the HADS anxiety subscale score was 4.2 at week 8 [110]. In addition, in a large acupuncture trial of cancer survivors, among 159 patients with baseline HADS anxiety subscale scores ≥8, the HADS anxiety subscale score SD was 4.0 during follow-up [155,156]. On the basis of these studies, it is assumed that the HADS anxiety subscale score SD will be approximately 4.2. Dividing the raw-score MCID of 1.7 points by 4.2 yields a standardized difference, that is, Cohen *d*=0.40. The noninferiority margin of Cohen *d*=0.35 SD is smaller than the standardized MCID (Cohen *d*=0.40) of the HADS anxiety subscale; as such, the noninferiority margin and statistical approach will find MT to be noninferior to CBT only if MT is not meaningfully worse than CBT.

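### The primary noninferiority contrast is a difference in change with no adjustment for baseline HADS anxiety: it is valid, but it gives up precision and is exposed to chance baseline imbalance

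*Protocol article*

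**What the plan says.** Under General Description, every mixed model "will model the outcome as a function of the treatment arm and assessment time (categorical), controlling for the randomization stratification variables" and "including a subject-specific random intercept". Under Aim 1, "the model will include all time points (categorical) at which the outcome was assessed (baseline and weeks 4, 8, 16, and 26"), and the comparison of arms rests on "specific coefficients from time-by-arm interactions added to the general LMM template". Inference is confined to the coefficients at weeks 8 and 26, "which are interpreted as the differences between arms in change from baseline to 8 and 26 weeks, respectively". The noninferiority test is made "within a noninferiority margin of 0.35 SD for both comparisons". The same approach is applied, as superiority tests, to fatigue, the other comorbid symptoms and quality of life.

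Three further facts matter. Randomization follows the baseline assessments, and its strata are site, anxiety medication and language, not anxiety severity (Randomization). Entry requires a HADS anxiety score of at least 8 (Eligibility Criteria). Power is computed from a two-sample t test on change scores, using an SD of 4.2 that comes from follow-up scores (Sample Size and Power).

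**The concern.** With baseline as an outcome row and an arm main effect in the model, the arm coefficient is a freely estimated baseline difference. Each week 8 or week 26 interaction is then a difference in change from baseline. The stratification factors enter as main effects that are constant over time, so they largely cancel from a change contrast and do not stand in for baseline anxiety.

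Because baseline is measured before randomization, the true baseline means are equal by design. Estimating them separately has two consequences:

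- **Precision.** The noise in the observed baseline difference is carried into the contrast, so the interval to be compared with the margin is generally wider than it need be.
- **Conditional error.** If one arm happens to start with higher anxiety, regression to the mean makes it appear to improve more. In a noninferiority comparison this can push the result in either direction.

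**Working it through.** **Inputs from the article.** 150 per arm and 15% attrition give 150 × 0.85 = 127.5 evaluable per arm. One-sided alpha is 0.025 per test. The margin is 0.35 SD with SD 4.2, that is 0.35 × 4.2 = 1.47 points.

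**Assumed, because the article does not give them.** Baseline SD s0, baseline-to-follow-up correlation r, and a true difference of 0. Follow-up SD s1 is taken as 4.2, and the margin is held at 1.47 points. The entry rule of 8 or more truncates the baseline distribution, so s0 of 2.5 to 3.2 is shown alongside s0 = 4.2.

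**Step 1: the plan's own figure.** With SD 4.2 applied to the change score, the t-test power is 79.5% (79.8% by the normal approximation). The stated 80% is reproduced.

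**Step 2: variance and power.** Per-participant variance of the change score: s0² + s1² − 2·r·s0·s1. Baseline-adjusted variance: s1²(1 − r²). The first exceeds the second by (s0 − r·s1)², which is never negative.

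Example, s0 = 3.2 and r = 0.3: change 10.24 + 17.64 − 8.064 = 19.816; adjusted 17.64 × 0.91 = 16.052; reduction 1 − 16.052/19.816 = 19%.

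| s0 | r | Change variance | Adjusted variance | Reduction | Power, change | Power, adjusted |
|---|---|---|---|---|---|---|
| 2.5 | 0.3 | 17.59 | 16.05 | 9% | 79.6% | 83.1% |
| 2.5 | 0.6 | 11.29 | 11.29 | 0% | 93.6% | 93.6% |
| 3.2 | 0.3 | 19.82 | 16.05 | 19% | 74.8% | 83.1% |
| 3.2 | 0.6 | 11.75 | 11.29 | 4% | 92.7% | 93.6% |
| 4.2 | 0.5 | 17.64 | 13.23 | 25% | 79.5% | 89.5% |

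**Step 3: shift from a chance imbalance.** The 95% limit of the baseline difference is 1.96 × s0 × √(2/150). The planned estimate moves by that amount times (1 − r·s1/s0), taking follow-up to be linear in baseline.

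| s0 | r | Imbalance at limit | Factor | Shift (points) | Share of 1.47 |
|---|---|---|---|---|---|
| 2.5 | 0.6 | 0.57 | −0.01 | about 0 | about 0% |
| 2.9 | 0.4 | 0.66 | 0.42 | 0.28 | 19% |
| 3.2 | 0.3 | 0.72 | 0.61 | 0.44 | 30% |
| 4.2 | 0.5 | 0.95 | 0.50 | 0.48 | 32% |

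**Step 4: the common-baseline constraint under the planned covariance.** Exact generalized-least-squares variances were computed for the five-visit model, with 150 per arm falling to 127.5 under an assumed monotone dropout pattern. The working covariance was the random intercept only. A sandwich variance was used where the true covariance differed from it. Ratios are variance with the constraint over variance without it.

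- Equal SDs of 4.2 and a truly constant correlation of 0.5: 0.77 to 0.78, so the gain is real.
- Baseline SD 3.0, follow-up SD 4.2: 0.86 at r 0.3, 0.95 at r 0.5, 1.01 at r 0.6, 1.06 at r 0.7.
- Baseline SD 2.5, same range of r: 0.92 to 1.12.

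Dropping the arm term and changing nothing else can therefore give no gain, or a small loss. The largest power loss found was about 1.5 points, in settings already above 90%.

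**The case against.** The strongest reply is that nothing in the plan is invalid. The estimand matches the model, the contrast is unbiased over randomizations, a free arm term does not affect the type I error, and the stated power is computed on change scores and reproduces without any fix. All of that stands.

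Three stronger readings are tempting, and the article does not support them:

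- **That the primary analysis is biased.** The error is conditional on the imbalance that happens to occur, and it averages to zero over randomizations. The figures in Step 3 are at the 95% limit, not at a typical imbalance.
- **That a constraint on the baseline means adds power for nothing.** Under the planned random-intercept covariance and a truncated baseline, it may not (Step 4).
- **That the plan itself implies a gain of about 10 points.** That figure needs a baseline SD of 4.2 and a correlation of 0.5. The article states neither. Its SDs are follow-up values, and the entry rule makes a smaller baseline SD plausible.

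It can also be said that the template allows further covariates and that the full analysis plan is not shown. That allowance is general and does not name baseline HADS. The article does spell out the primary model, and as written the model does not adjust for baseline. Whether a fuller document does so cannot be seen here.

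**Conclusion.** The point holds as a missed efficiency and an avoidable sensitivity, not as an error of validity. Full baseline adjustment reduces the contrast variance by 0 to 19% for baseline SD 2.5 to 3.2 and r 0.3 to 0.6, worth 0 to about 8 power points. The reduction is 25%, about 10 points, if baseline SD is 4.2 and r is 0.5. Over the same scenarios, a baseline imbalance at its 95% limit shifts the planned estimate by 0 to 32% of the margin. These results rest on follow-up SD 4.2, a margin fixed at 1.47 points, 127.5 evaluable per arm and a true difference of 0. Baseline SD and correlation are assumptions throughout, so the benefit for this trial could lie anywhere in these ranges, including near zero.

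**What to change.** Specify one of two models for HADS anxiety, and the same for fatigue and the other repeated outcomes:

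- Model the four post-baseline visits, with baseline score and baseline-by-visit as covariates; or
- Keep baseline as an outcome but drop the arm main effect, leaving arm-by-time terms at the four post-baseline visits only, so that the arms share a baseline mean.

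In either case, replace the random-intercept-only covariance with an unstructured one. This is part of the fix, because the constraint alone may not help when the baseline is truncated. Keep the margin in points, so that it does not shrink with the residual SD.

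The week 8 and week 26 treatment contrasts keep their meaning. The cost is a change to the mean model and to the covariance specification, made before any unblinded analysis. No new data are needed and the sample size is unchanged.

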### Randomization

After completing the baseline assessments, participants will be randomized using MSK’s secure computer system that ensures full allocation concealment. Randomization will be 1:1 (MT:CBT) using randomly permuted blocks of random length, which are stratified by study site, current anxiety medication use (yes or no), and preferred language (English or Spanish). The principal investigator and biostatistician will be blinded to treatment assignments.

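### The fixed .025/.025 split between the two primary noninferiority tests is valid, but Holm's step-down rule would add about 4 to 5.5 points of power per week at the same overall error

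*Protocol article*

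**What the plan says.** Under Aim 1—Hypotheses 1(a) and 1(b), the protocol article states that "the 2 primary end points are HADS anxiety score changes at 8 weeks and 26 weeks". Each is tested at P<.025 "for each comparison, controlling the overall type I error at" .05. The Sample Size and Power section gives the sidedness, "a 1-sided significance threshold of *P*=.025 (controlling the overall type I error at 0.05 for our 2 primary end point comparisons", and bases 80% power per test on that threshold, "each with a noninferiority margin of Cohen *d*=0.35 SD for both comparisons". Neither section mentions a step-down rule, reuse of the error rate after a success, or an order of testing. The two sections agree with each other.

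**The concern.** Two tests at a fixed .025 each are a plain Bonferroni split of an overall .05. Once noninferiority has been shown at one week, the plan makes no further use of that week's share of the error rate. Holm's rule does: the smaller one-sided P is compared with .025 and, if it passes, the other is compared with .05. Overall control at .05 holds whatever the correlation between the weeks, and nothing that the fixed split would reject is lost.

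At stake is some avoidable risk of failing to show noninferiority at one of the weeks when the treatments are truly equal, in a trial planned at about 80% power per test. The more powerful rule needs no extra participants, visits or data.

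**Working it through.** **Inputs from the article**
- Sample size (Sample Size and Power): "Assuming 150 participants are randomized to each arm, 15% attrition". Analysed per arm: 150 × 0.85 = 127.5.
- Allocation (Randomization): 1:1.
- Margin: 0.35 SD at both weeks.
- Threshold: one-sided .025 per test, .05 overall.

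**Assumptions**
- The true difference is 0 at both weeks.
- The correlation ρ between the two test statistics is not given. The planned model has a subject-specific random intercept (General Description), which implies compound symmetry. Two change scores that share a baseline then have variance 2σ² each and covariance σ², where σ² is the residual variance, so ρ = 0.5. The range 0.3 to 0.8 is used, with higher values also shown.

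**Step 1: the plan's own figure**
- Standard error in SD units: √(2/127.5) = 0.1252.
- Mean of each test statistic: 0.35/0.1252 = 2.795.
- Power per test: Φ(2.795 − 1.960) = 0.798. The noncentral t gives 0.795.

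The stated 80% reproduces.

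**Step 2: power per week under Holm**

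Let Z₁ and Z₂ be bivariate normal with means 2.795, unit variances and correlation ρ. Power at week 1 is

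P(Z₁ > 1.960) + P(1.645 < Z₁ ≤ 1.960 and Z₂ > 1.960).

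The second term is the gain. At ρ = 0.5, P(Z₁ > 1.645, Z₂ > 1.960) = 0.7347 and P(both > 1.960) = 0.6844. The gain is 0.7347 − 0.6844 = 0.0502 after rounding, and power is 0.798 + 0.050 = 0.848.

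| ρ | Fixed split, per week | Holm, per week | Gain (points) | At least one week, either rule |
|---|---|---|---|---|
| 0.3 | 79.8% | 85.3% | 5.5 | 93.3% |
| 0.5 | 79.8% | 84.8% | 5.0 | 91.2% |
| 0.7 | 79.8% | 84.3% | 4.5 | 88.6% |
| 0.8 | 79.8% | 83.9% | 4.1 | 86.9% |
| 0.9 | 79.8% | 83.3% | 3.5 | 84.8% |
| 0.95 | 79.8% | 82.7% | 2.9 | 83.4% |

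Simulation with 1,000,000 draws agrees at ρ = 0.5 (84.8%) and ρ = 0.8 (83.9%). The last column is the same under both rules because Holm's first step is the Bonferroni test.

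**Step 3: error control**

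If both nulls are true, a false claim requires the first step to reject, so the error equals that of the fixed split and is at most .05. If one week is at the margin and the other is truly equal, the Holm error is .025 + P(1.645 < Z₁ ≤ 1.960, Z₂ > 1.960) with Z₁ centred at 0 and Z₂ at 2.795. This gives 4.8% at ρ = 0.3, 4.9% at 0.5 and 5.0% at 0.8.

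**Step 4: unequal effects**

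If music therapy is worse by 0.05 SD at week 26 only, with ρ = 0.5, the gain is 3.6 points at week 8 and 7.7 points at week 26.

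**The case against.** The strongest reply is that nothing here is wrong. The split is prespecified, valid and consistent with the sample size, and its 80% is right. All of that stands. A reader might infer that the plan miscontrols its error rate or is underpowered for its own rule; the documents support neither.

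The gain also has a price. Every claim that Holm adds has a one-sided P between .025 and .05, so its two-sided 95% interval crosses the 0.35 SD margin. The fixed split holds both weeks to one standard, with intervals that match the decisions. This stands as a cost of reporting and interpretation, and a sponsor could reasonably prefer the simpler rule. It does not alter the fact that Holm meets the overall error rate that the article itself sets.

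The Sample Size and Power section calls its figure conservative, because the mixed model should have slightly higher power. If the effective SD were 5% to 10% smaller (an assumption), power per test would be 83.7% to 87.4% and Holm would add 3.1 to 4.9 points for ρ of 0.3 to 0.8. The gain shrinks but remains.

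A stronger reading would use the probability of success at both weeks, which rises from 68.4% to 78.5% at ρ = 0.5. That figure decides the matter only if success requires both weeks. Hypothesis 1(a) does name both, but the article states no such rule, and dividing the error rate between the tests fits separate claims. Under a both-weeks rule no split would be needed: testing each week at .05 gives 79.4% at ρ = 0.5, slightly more than Holm. The larger figure is therefore no argument for Holm.

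Lastly, the Results section reports 151 participants enrolled by January 2023, so a change would come mid-trial. It needs an amendment with a stated reason.

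**Conclusion.** The point holds as an efficiency improvement, not as an error. At the article's own overall one-sided .05, Holm raises power per week from 79.8% to between 83.9% and 85.3%, a gain of 4.1 to 5.5 points. This rests on no true difference at either week, 127.5 analysed per arm and ρ between 0.3 and 0.8. The gain is about 5 points at the value that the random-intercept model implies and falls to 2.9 points at ρ = 0.95. Holm helps only when one week passes .025 and the other falls between .025 and .05; it cannot rescue a trial that misses at both weeks.

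**What to change.** In Aim 1—Hypotheses 1(a) and 1(b), replace the threshold sentence with wording such as: the two one-sided noninferiority P values will be tested by Holm's step-down procedure at an overall one-sided .05, the smaller against .025 and, if it is significant, the other against .05. Add that Holm-adjusted P values will be reported beside the two-sided 95% intervals, and that any week declared at the .05 step is supported by a two-sided 90% interval while its 95% interval crosses the margin. In Sample Size and Power, 80% can stay as the approximate lower bound per test.

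The cost is a dated, documented amendment made before unblinding, matching wording in the analysis plan, and a less simple link between intervals and decisions. Sample size, visits and data collection do not change. If unblinding has already taken place, the fixed split should stay. If the sponsor intends success to require both weeks, the article should say so; each week can then be tested at the full overall level and Holm is not needed.

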#### Missing Data

As the only certain way to avoid biases from missing data is to collect complete data [152], the study team will strive to minimize missing observations by using study procedures that reduce participant burden. Participants who experience difficulties completing assessments on the web will have the option to complete assessments on paper or over the telephone with the research staff. Participants with time constraints or other barriers to completing outcome assessments will be given the option to complete only the primary outcome, that is, the HADS scale. Participants who withdraw from treatments will be encouraged to continue completing the outcome assessments. Reasons for withdrawal will be recorded for those who completely withdraw from the study. Given that missing data are inevitable in a prospective study, sensitivity analyses will be performed to assess the impact on the results of adjusting for patient disease progression or death, and analytical strategies that are as robust as possible to data losses will be applied. The study team will first explore whether missingness is associated with observed variables (eg, randomization arm and baseline outcome measures) by comparing patients with complete and incomplete data. Notably, the LMMs described previously will include patients with incomplete data under the missing at random assumption. However, the exploration of the data may deem the missing at random assumption to be inappropriate. Multiple imputation and pattern mixture models are well-established methods for addressing these issues [153,154]. Sensitivity analyses will be performed to evaluate the robustness of the LMM results by refitting the models after imputing the missing week 8 and week 26 outcomes using multiple imputation.

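### The recurrence sensitivity analysis removes whole participants, so a recurrence after week 8 also deletes a valid week 8 score recorded before it

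*Protocol article*

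**What the plan says.** The Aim 1 section expects that "a small number of cancer survivors may experience disease recurrence during the 26-week study" and plans sensitivity analyses "excluding those individuals who experienced a recurrence during the study period". It adds: "These sensitivity analyses will not replace the primary analysis".

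Three other statements bear on the rule:

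- The same section says that "the 2 primary end points are HADS anxiety score changes at 8 weeks and 26 weeks", so week 8 is a decision point in its own right.
- The General Description sets an intention-to-treat principle, under which "participants will be analyzed according to their randomly assigned treatment group regardless of dropout or treatment adherence status".
- The Missing Data section says that "the LMMs described previously will include patients with incomplete data under the missing at random assumption". The planned model can therefore use a participant who contributes some visits but not others.

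**The concern.** The exclusion is defined by person and by an event at any time in the study period, not by visit. A participant who recurs in week 20 has by then given baseline, week 4, week 8 and week 16 scores, none of them affected by the recurrence. The rule removes all four.

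Two things follow. Precision is lost at week 8 with no gain there, because those scores do not contain the influence that the analysis is meant to remove. The week 8 comparison is also made among people selected by something that happens after randomisation and, for later recurrences, after week 8 itself. A difference from the primary week 8 result could then come from removing scores affected by recurrence, or from removing people whose week 8 scores were sound. The check is meant to isolate the first.

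**Working it through.** **Inputs from the article (Sample Size and Power):** 150 per arm, 15% attrition, margin 0.35 SD, one-sided threshold 0.025, assumed SD 4.2 points, stated power 80%. **Not in the article:** any recurrence rate, its timing, or how much worse people score after recurrence. Values for these below are assumptions.

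**1. The stated power.** Evaluable per arm: 150 × 0.85 = 127.5. Power = Φ(0.35 × √(127.5/2) − 1.96) = Φ(0.835) = 79.8% (79.5% with the noncentral t). The stated 80% is reproduced.

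**2. Week 8 scores lost.** If recurrences fall evenly over 26 weeks, the share after week 8 is (26 − 8)/26 = 69%. With 3% to 6% of 300 recurring (9 to 18 people), 0.69 × 9 to 0.69 × 18 gives about 6 to 12 people. After 15% attrition (× 0.85), about 5 to 11 of them would have a week 8 score to lose.

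**3. Precision of the sensitivity analysis.** The same power formula after excluding a share r of evaluable participants:

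| r (assumed) | evaluable per arm, 127.5 × (1 − r) | power |
|---|---|---|
| 0 | 127.5 | 79.8% |
| 2% | 125.0 | 79.0% |
| 5% | 121.1 | 77.8% |
| 10% | 114.8 | 75.5% |

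If pre-recurrence scores are kept and timing is even, only the 8/26 of recurrences before week 8 cost a week 8 score. At r = 5% this leaves 127.5 × (1 − 0.05 × 8/26) = 125.5 per arm, and Φ(0.35 × √(125.5/2) − 1.96) = Φ(0.813), about 79.2%. If all recurrences come after week 8, the full 79.8% is retained.

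**4. Shift in the contrast.** Suppose a share r of an arm recurs and scores D SD worse than the rest of that arm. Excluding them lowers the arm mean by r × D. With the same D in both arms, the MT − CBT contrast moves by −(r_MT − r_CBT) × D.

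| recurrence, MT vs CBT (assumed) | shift at D = 0.5 SD | shift at D = 1.0 SD | share of 0.35 SD margin |
|---|---|---|---|
| equal | 0 | 0 | 0 |
| 6% vs 4% | 0.01 SD | 0.02 SD | 3% to 6% |
| 8% vs 2% | 0.03 SD | 0.06 SD | 9% to 17% |

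In points, the margin is 0.35 × 4.2 = 1.47 and the largest shift shown is 0.06 × 4.2 = 0.25. These values of D are plausible for scores taken after recurrence, so they bear mainly on week 26. They cannot simply be applied to week 8 scores recorded before recurrence. At week 8 the main harm is the data loss in steps 2 and 3.

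**The case against.** The strongest defence is that the analysis is supportive, is expressly barred from replacing the primary one, and concerns few people. The primary analysis remains intention to treat. Nothing in the article suggests that seven sessions of one therapy rather than the other would change recurrence within 26 weeks. If arm does not affect recurrence, the never-recurrent groups stay comparable in expectation, and the analysis answers a clear question about people without recurrence. The alternative also has a price: it sets observed post-recurrence scores aside and asks a somewhat different question. All of this stands. It limits the size of the point, but it does not explain why scores recorded before the event should be thrown away.

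A reader might infer three stronger points, which the article does not support:

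- **That a second analysis enters progression or death as covariates.** The Missing Data section says only that "sensitivity analyses will be performed to assess the impact on the results of adjusting for patient disease progression or death". It names no mechanism, and the detail may properly sit in an analysis plan that is not shown.
- **That the two sections contradict each other.** One concerns recurrence in the Aim 1 comparison, and the other progression or death under missing data. Two supplementary analyses with different purposes can coexist.
- **That the recurrence analysis cannot be interpreted.** Step 4 gives no shift when recurrence is equal between arms. The result is less precise and somewhat harder to read, but it is not meaningless.

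**Conclusion.** The point holds in a narrow form and is minor. As worded, the rule drops participants from the week 8 comparison for a later event, although the planned model could keep their earlier scores. Under the assumed 3% to 6% recurrence with even timing, about 5 to 11 week 8 scores are lost. Under assumed exclusions of 2% to 10%, power in this supportive analysis falls from 79.8% to between 79.0% and 75.5%. Any shift in the contrast needs unequal recurrence between arms and reaches at most 17% of the margin in the cases tried, mainly at week 26. All these sizes rest on assumed rates, since the article says only that few recurrences are expected. No primary estimate, test, margin or power figure changes.

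**What to change.** In the Aim 1 section, replace the person-level exclusion with a visit-level rule for this sensitivity analysis: keep every randomised participant and all HADS scores up to recurrence, set only scores after recurrence to missing, and refit the planned linear mixed model.

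The cost is one sentence and no new outcome data. The date of recurrence is needed for each affected participant, and placing a recurrence within the study period already requires knowing roughly when it occurred. The downside is the assumption that scores after recurrence are missing at random given the earlier ones, which should be stated alongside the result.
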